### Data collection and management

Within the OPTIMIST Investigator Team at each site, nominated personnel (e.g. Unit Data Collectors, Unit Research Nurses) collect data and enter it onto hard copy and/or electronic forms, as available. Data management is coordinated from the Clinical Epidemiology and Biostatistics Unit (CEBU) at the Murdoch Childrens Research Institute (MCRI), using a web-based database management system.

#### Data collection in hospital

Basic demographic, perinatal, and clinical data, as well as in-hospital outcomes, are collected prospectively for each patient, starting at enrolment. The data are entered on a hard copy clinical report form. Data pertaining to the MIST procedure are collected by the OPTIMIST Treatment Team, on a separate randomisation and intervention form. This form is not seen by other clinical or research staff. Once filled in, it is sent electronically to CEBU at MCRI. Information recorded includes the number of attempts required to catheterise the trachea, the total time taken, the lowest heart rate noted during the MIST procedure and time for restoration of heart rate above 100 beats per minute, the lowest SpO_2_ noted and time for restoration of SpO_2_ above 80%, and the need for and duration of positive pressure inflations by mask.

Data on heart rate, CPAP pressure, FiO_2_, and SpO_2_ prior to, and at four hours after intervention are collected, along with the results of pre- and post-intervention blood gas analysis.

#### Follow up

Each infant will have a full clinical and neurological assessment performed at 2 years by a developmental paediatrician blinded to the initial randomisation. Psychometric testing will be performed by a trained practitioner using the Bayley III Scales of Infant Development (or equivalent). Hospitalisation history in the first two years will be documented at this visit.

### Outcome variables

#### Primary outcome

Incidence of composite outcome of death or physiological BPD [42].

#### Secondary outcomes

A range of standard clinical outcomes pertaining to the first hospitalisation are being ascertained in trial participants. These are shown in Table 1. Additionally, data are being collected in the intervention group relating to the applicability and safety of the Hobart method (Table 2). For this purpose, data from the study oximeter are used alongside data recorded manually by the Treatment Team. Finally, longer term outcomes are being evaluated at two years corrected age as part of the OPTIMIST-A follow-up study. This study will have its own protocol and funding stream. Selected outcomes from this study are shown in Table 3.

**Table 1 T1:** Clinical outcomes during first hospitalisation

Physiological BPD [42]	Duration of intubation (all episodes)
Clinical BPD (oxygen or positive pressure support at 36 weeks corrected gestation) [45]	Duration of CPAP/NIPPV (all episodes)
Mild/moderate/severe BPD [45]	Duration of intubation and CPAP
Death	Duration of HFNC, minimum flow rate 2 L/min
Death or BPD (clinical definition)	Duration of respiratory support
Intraventricular haemorrhage (IVH) (all grades)	Duration of oxygen therapy
IVH grades III and IV [46]	Requirement for oxygen at home
Cystic periventricular leukomalacia	Length of stay in intensive care
Retinopathy of prematurity (ROP) > stage II	Length of hospital stay
Major morbidity (any of IVH grade III or IV, periventricular leukomalacia, ROP > stage II, physiological BPD) [47]	Total hospital billings
Death or major morbidity	Calculated cost of hospitalisation
NEC (Modified Bell stage 2 or greater) [48]	Pneumothorax requiring drainage
NEC or spontaneous intestinal perforation requiring surgery	Pulmonary haemorrhage
Requirement for intubation < 72 h	Patent ductus arteriosus (PDA) requiring anti-prostaglandin therapy
Requirement for intubation at any time	PDA requiring ligation
Need for additional surfactant therapy	Late onset sepsis (positive bacterial or fungal culture from a normally sterile site)
Overall number of surfactant doses (including that given by MIST)	Time to regain birth weight

**Table 2 T2:** Applicability and safety outcomes in infants randomised to receive surfactant via the Hobart method

Incidence of successful surfactant administration via MIST	Duration of hypoxaemia (SpO_2_ < 80%)
Number of catheterisation attempts	Requirement for, and duration of, positive pressure ventilation by mask
Duration of bradycardia (heart rate < 100 beats per minute)	Incidence of apparent discomfort

**Table 3 T3:** Selected outcomes from the OPTIMIST-A follow-up study

Number of hospitalisations in the first 2 years	Major disability at 2 years
Number of hospitalisations with respiratory illness in the first 2 years	Death or major disability at 2 years

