### Intervention – standard care (sham MIST procedure)

The following protocol is used in the standard care group:

1. Position the infant as for a standard intubation procedure. This is the only actual intervention for babies randomised to standard care. CPAP is not interrupted at any time in this group. The OPTIMIST oximeter is used and standard monitoring disconnected as for the MIST procedure.

2. Simulate the MIST procedure in terms of time taken and movement and communication within the screened area.

3. After the procedure, restore the infant to their previous position, and ensure the CPAP settings are the same as prior to the sham procedure.

4. Record the time of the sham intervention on the OPTIMIST Intervention Form, remove the form from the bedside, and send to the Data Management Centre, retaining a copy, exactly as described for the MIST procedure above.

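### Peri-procedural bradycardia, hypoxaemia and mask ventilation are defined as outcomes in the MIST arm only, so their randomised excess over background cannot be estimated, although sham infants wear the same study oximeter

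*Protocol article*

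**What the plan says.** The abstract lists safety of the Hobart method among the secondary outcomes. Under Secondary outcomes, the article says that "data are being collected in the intervention group relating to the applicability and safety of the Hobart method", and Table 2 carries the title "Applicability and safety outcomes in infants randomised to receive surfactant via the Hobart method". The table holds two kinds of item. Successful administration and number of catheterisation attempts exist only where a catheter is passed. Duration of bradycardia (heart rate below 100 per minute), duration of hypoxaemia (SpO2 below 80%), mask ventilation and apparent discomfort could occur in any infant. On the source, "data from the study oximeter are used alongside data recorded manually by the Treatment Team".

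In the sham arm, the infant is positioned as for intubation and CPAP is not interrupted. Of the positioning, the text says "This is the only actual intervention for babies randomised to standard care". On monitoring, it says "The OPTIMIST oximeter is used and standard monitoring disconnected as for the MIST procedure". The Masking section asks that the time taken be the same in both arms. The sham steps then give one item to write down: "Record the time of the sham intervention on the OPTIMIST Intervention Form".

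Under Data collection in hospital, "Data pertaining to the MIST procedure are collected by the OPTIMIST Treatment Team, on a separate randomisation and intervention form"; the items listed include lowest heart rate and SpO2, recovery times and mask inflations. The same section adds, without limiting it to one arm, "Data on heart rate, CPAP pressure, FiO_2_, and SpO_2_ prior to, and at four hours after intervention are collected".

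**The concern.** The trial creates a randomised control period: same device, same positioning, same screening, matched duration. The outcome definitions then leave that control out of the procedural safety results.

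This matters because the background is unlikely to be nil. By the entry criteria these infants have respiratory distress and need FiO2 of at least 0.30, and the intubation criteria provide for repeated apnoea needing vigorous stimulation. Some will have bradycardia or desaturation during a period of handling, whichever arm they are in. A rate or duration seen only in the MIST arm mixes that background with the effect of laryngoscopy, catheterisation and surfactant. A reader weighing benefit against procedural harm needs the difference, and the design could supply it at little cost.

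**Working it through.** **Figures in the article.** The article states no figure for this comparison. The inputs taken from it are:
- 303 infants randomised per arm (Sample size). This reproduces. For 38% against an exact one-third reduction (25.33%), 90% power and two-sided 5%, the usual two-proportion formula gives 281.3. The continuity correction n/4 × [1 + √(1 + 4/(n·d))]², with d = 0.1267, gives 296.9, rounded up to 297. Then 297/0.98 = 303.06 and 297 × 1.02 = 302.94, so 303 follows to the nearest integer.
- Bradycardia in 11 of 25 infants, 11/25 = 44% (Clinical experience with the Hobart method). The series was uncontrolled, covered 25–34 weeks, used about 100 mg/kg and gave no premedication.

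**Assumption.** The article gives no background rate for sham infants. A range of 0% to 30% is assumed.

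**What one arm gives.** Half-width = 1.96 × √(0.44 × 0.56/303) = 1.96 × 0.0285 = 0.056. The report would be 44% (95% CI 38.4% to 49.6%), whatever the background.

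**What two arms would give.** Excess = 0.44 − p₀, with half-width 1.96 × √(0.44 × 0.56/303 + p₀(1 − p₀)/303). At p₀ = 0.10 this is 1.96 × √(0.000813 + 0.000297) = 0.065.

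| Assumed sham rate p₀ | Excess, points (95% CI) | Excess as share of 44% |
|---|---|---|
| 0% | 44 (38.4 to 49.6) | 100% |
| 5% | 39 (32.9 to 45.1) | 89% |
| 10% | 34 (27.5 to 40.5) | 77% |
| 20% | 24 (16.8 to 31.2) | 55% |
| 30% | 14 (6.4 to 21.6) | 32% |

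The same one-arm result of 44% is compatible with every row. Power to detect the difference at 303 per arm is about 95% at a sham rate of 30% and higher at the lower rates, so the existing sample is large enough. The illustration uses incidence. Table 2 lists durations for bradycardia and hypoxaemia, and the same reasoning applies to them, but the article gives no figures from which to size it.

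**The case against.** The strongest reply is that Table 2 describes how a technique performs, and a one-arm description suits that purpose. Attempts and success have no sham counterpart. Because the sham is positioning alone with CPAP uninterrupted, events during laryngoscopy can be tied to it in time. The initial Hobart series did this for bradycardia, which mostly coincided with insertion of the blade. Pre-intervention observations give each infant a baseline. Clinical harms such as pneumothorax, pulmonary haemorrhage, intraventricular haemorrhage and death are in Table 1, which covers all trial participants.

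Much of this stands. A reader might infer that bradycardia and hypoxaemia cannot be attributed to the procedure at all; the timing information shows that this goes too far. What it does not supply is the size of the excess. The initial series reports no such timing for hypoxaemia, and single observations before the intervention and at four hours cannot give durations over the procedure.

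Three other inferences are not supported either:
- That sham traces are discarded, or already held and ignored. The article does not say whether they are stored.
- That the form for sham infants holds the time and nothing else. The time is the only item named in the sham steps, but the form is not shown.
- That the DSMC is deprived of a safety contrast. Its remit includes adverse events, its charter is not shown, and nothing says that Table 2 limits what it sees.

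The 44% is also a weak guide to this trial, which enrols 25–28 weeks, specifies 200 mg/kg and allows atropine. It serves here only to show how far the answer depends on the missing comparator.

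**Conclusion.** The point holds as a design weakness that is cheap to remedy. It is not an error or contradiction. The restriction to one arm is a stated outcome definition, so it is not a detail left to an analysis plan. As defined, Table 2 yields a raw MIST rate with a precision of about ±6 points if the rate is 44%, and no estimate of the randomised excess. Over the assumed sham range of 0% to 30% that excess would run from 44 down to 14 points. The conclusion that the excess cannot be estimated does not depend on those values; the size does, and it rests on an assumed background and on a rate from 25 infants in a wider gestational range. The point concerns bradycardia, hypoxaemia and mask ventilation. It does not touch catheterisation attempts or success, and it leaves the primary outcome unaffected.

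**What to change.** 1. State that study-oximeter data are retained for sham infants as well as MIST infants.
2. Report incidence and duration of bradycardia (below 100 per minute) and of hypoxaemia (SpO2 below 80%) in both arms, from the oximeter, over one window: from connection of the study oximeter to 5 minutes after the procedure. The start of screening would not serve, because the infant is screened before randomisation and the MIST steps connect the oximeter only during preparation. The 5-minute observation is written under the MIST steps, so the same end point should be stated for the sham.
3. Record mask ventilation on the intervention form in both arms.
4. Base the bradycardia and hypoxaemia comparison on the oximeter. The Treatment Team knows the allocation, so its manual records are open to bias. For the same reason, apparent discomfort is better left descriptive.
5. Keep catheterisation attempts and successful administration as MIST-only outcomes.
6. Make the two-arm comparison available to the DSMC.

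The cost is outcome wording, a few form fields and device downloads for sham infants, with no change to sample size. The sham data should leave the bedside by the same concealed route as the intervention form, to protect masking. Retention should be settled during recruitment, because traces that are not saved cannot be recovered later.

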### Statistical analysis and reporting

#### Statistical analysis

Data handling, verification and analysis for the OPTIMIST-A trial are being performed by CEBU at MCRI. Statistical analysis will follow standard methods for randomised trials and the primary analysis will be by intention to treat. For dichotomous outcomes, including the primary outcome in OPTIMIST-A, proportions will be compared using the odds ratio with 95% CI, obtained from a logistic regression analysis with adjustment for the strata (defined by centre and gestational age category) used in the randomisation. Continuous outcomes will be compared using differences between mean values, estimated from normal linear regression models with the same stratification adjustments. Secondary analyses will use expanded regression models to explore potential confounding effects of chance imbalances between arms in birth weight, gender, antenatal steroids, or mode of delivery. In further secondary analysis, we will explore evidence for heterogeneity of effects between the two gestational age strata in the trial, using interaction tests and subgroup analyses.

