### Important considerations in trial protocol development

#### Enrolment criteria

Not all preterm infants 25–28 weeks gestation managed on CPAP from the outset stand to benefit from surfactant administration with a minimally-invasive technique. Some have minimal or mild RDS, and are well supported by CPAP alone. For MIST to be of value, it must be coupled with early and accurate selection of infants at greatest risk of failing CPAP. In this regard, several indicators previously put forward have been rejected: a) radiological scores [6], which are confounded by variability of X-ray technique and subjectivity of interpretation, b) functional surfactant assays [37,38], which require specialised equipment and training, c) indices of oxygenation based on arterial pO_2_[6], which are impractical because so few infants on CPAP have arterial lines *in situ*, and d) Silverman clinical scores, which will vary considerably depending on the CPAP pressure level.

Using data from the RHH-RWH preterm CPAP cohort, we sought a bedside predictor of early CPAP failure in the early post-natal period in infants 25–28 weeks gestation. In a logistic regression model incorporating demographic variables, FiO_2_ and CPAP pressures, by far the strongest predictor of later need for intubation was the highest FiO_2_ in the first 2 hours. Addition of CPAP pressure improved the goodness of fit only slightly (R^2^ 0.5 vs 0.45). A similar regression analysis by De Jaegere et al. in infants <30 weeks gestation found FiO_2_ by 2 hours to be the most influential variable in prediction of later intubation [39]. Area under the receiver operating characteristic curve for prediction of CPAP failure using FiO_2_ was 0.83 in the RHH-RWH preterm CPAP cohort and 0.84 in the study of De Jaegere et al. [39]. On this basis, and in recognition of the need for simplicity in framing the entry criteria, highest appropriate FiO_2_ has been chosen as an entry criterion for the OPTIMIST-A trial. The FiO_2_ threshold of ≥0.30 is the same as that used in the AMV trial, and in our preterm CPAP cohort predicted intubation <72 hrs with a sensitivity of 83% and positive predictive value of 60%. Infants achieving this threshold in the first 2 hrs had a relatively high likelihood of later intubation (OR 5.6, 95% CI 1.7-18).

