### Sample size

In the RHH-RWH CPAP study, amongst infants of 25–28 weeks gestation the proportion positive for the outcome of death or BPD was 53% in those failing CPAP and 38% in those reaching the OPTIMIST-A enrolment threshold in the first 2 hours. A reduction by one-third in the proportion of infants with this outcome (i.e. from 38% to 25%) would be a major advance in care for this patient group, relieving the burden at both individual and NICU levels. Detection of a reduction of this magnitude with 90% power and α = 0.05 (two-sided) would require 297 subjects per arm [49]. An allowance has been made for withdrawal of 2% of subjects post-recruitment. The number of subjects to be randomised in each arm is thus 303, for an overall total of 606.

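### The primary model leaves out baseline predictors the trial collects, early FiO2 among them: a valid analysis that misses a modest, nearly free gain in precision

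*Protocol article*

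**What the plan says.** The Statistical analysis section of the protocol article sets the primary comparison of death or physiological BPD as an odds ratio from logistic regression. The only adjustment is for the randomisation strata: centre, and gestation as 25–26 or 27–28 weeks. Secondary analyses then use "expanded regression models to explore potential confounding effects of chance imbalances between arms in birth weight, gender, antenatal steroids, or mode of delivery". No other baseline variable is named in a model.

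Two other places bear on this. Under Enrolment criteria, the sponsor's own cohort analysis found that "by far the strongest predictor of later need for intubation was the highest FiO_2_ in the first 2 hours", with an AUC of 0.83 for CPAP failure. Under Data collection in hospital, "Data on heart rate, CPAP pressure, FiO_2_, and SpO_2_ prior to, and at four hours after intervention are collected". So FiO2 is ranked first as a predictor of intubation and is recorded, but it appears in neither the primary nor the secondary models.

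**The concern.** Randomisation already protects the comparison from systematic confounding. The reason to adjust for a baseline variable is that it predicts the outcome, and that reason does not depend on how balanced the arms turn out to be. In logistic regression, adjusting for a prognostic covariate moves the treatment log odds ratio further from zero than it inflates its standard error, so power rises without another infant being recruited.

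The plan gives the weaker reason and places the variables accordingly: they serve to probe imbalance after the fact and do not sharpen the main result. Gestation is cut to two levels although eligibility is set in weeks and days. At stake is precision, chiefly if the true effect is smaller than the one-third reduction the trial was sized for.

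**Working it through.** **Inputs from the article.** Control risk: "38% in those reaching the OPTIMIST-A enrolment threshold in the first 2 hours". Target: a one-third reduction, written as 25% (unrounded 0.38 × 2/3 = 25.33%). Size: "90% power and α = 0.05 (two-sided) would require 297 subjects per arm". Withdrawal allowance 2%. For FiO2: AUC 0.83 for CPAP failure, and 60% positive predictive value for intubation before 72 hours at FiO2 of 0.30 or more. Death or BPD was 53% after CPAP failure and 14% after CPAP success.

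**Input not in the article.** How well any baseline variable predicts death or BPD. This is assumed below and varied.

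**1. The plan's own figure.** For two proportions with p1 = 0.38, p2 = 0.2533, mean 0.3167 and difference d = 0.1267:

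n = [1.960 √(2 × 0.3167 × 0.6833) + 1.282 √(0.38 × 0.62 + 0.2533 × 0.7467)]² / d² = (1.289 + 0.835)² / 0.01604 ≈ 281.3

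With the Fleiss continuity correction: (281.3/4) × [1 + √(1 + 4/(281.3 × 0.1267))]² ≈ 296.9, so 297. The stated figure is reproduced. 297 × 1.02 = 302.9 gives 303 per arm, 606 in total.

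Without the correction, 297 per arm has 91.5% power at 25.33% and 92.9% at 25%. The plan is not short of power for its target.

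**2. What FiO2 alone could contribute.**

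- Implied event rate at the threshold: 0.60 × 0.53 + 0.40 × 0.14 = 0.374, close to the stated 38%.
- P(CPAP failure | event) = 0.318/0.374 = 0.85.
- P(CPAP failure | no event) = (0.60 × 0.47)/0.626 = 0.45.
- If FiO2 affects death or BPD only through CPAP failure, its AUC for death or BPD is 0.5 + (0.85 − 0.45) × (0.83 − 0.5) ≈ 0.63.

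The 0.83 comes from a cohort not restricted to FiO2 of 0.30 or more. Within the trial the range is cut, so 0.63 is an upper figure under this assumption.

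**3. Gain in power from adjustment.** Simulated trials of 297 per arm, 4,000 per setting, used a Wald test from logistic regression with and without one normally distributed baseline score. Marginal risks were held fixed. Centre and gestation strata were not simulated.

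| Log-odds SD of score | AUC (approx.) | 38% v 25%: without → with | 38% v 28%: without → with |
|---|---|---|---|
| 0.5 | 0.64 | 92.6% → 93.5% | 74.2% → 76.2% |
| 0.7 | 0.67 | 92.9% → 94.6% | 73.8% → 77.6% |
| 1.0 | 0.73 | 92.9% → 96.3% | 73.5% → 81.3% |

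The gains are 0.9, 1.7 and 3.4 points at the planned effect, and 2.0, 3.8 and 7.8 points at the smaller one. A repeat simulation gave about 1, 1.5 and 3 points, and about 1.5, 3 and 7 points. FiO2 alone corresponds at best to the first row.

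**4. What adjustment costs.** Adding four covariates with no prognostic value lowered power by at most about 0.4 points. The odds ratio changes meaning: the marginal value is (0.25/0.75)/(0.38/0.62) = 0.544, and conditional on the score it is 0.527 at SD 0.5 and 0.485 at SD 1.0. Expected events are 297 × (0.38 + 0.25) ≈ 187.

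**The case against.** The strongest reply is that nothing here is wrong. Intention to treat with adjustment for the randomisation strata is a sound primary analysis, gestation is already in it, and power exceeds 90% without further covariates. That stands. A reader might infer that the result is biased or the trial underpowered; step 1 supports neither.

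A reader might also infer that the expanded models offer a second result to choose from once imbalance is seen. The article labels them secondary and names their four covariates, so they do not compete with the primary estimate. It is also tempting to carry the AUC of 0.83 over to the primary outcome, or to call all the omitted variables strong predictors. The article documents strength only for FiO2, only for intubation, and for the highest value in the first 2 hours, whereas infants may enter up to 6 hours of age. It gives no prognostic strength for birth weight, sex, steroids or mode of delivery, and part of what birth weight carries may already be in the gestation band. Nor is FiO2 unused in the trial: it is an entry criterion. It is absent only from the stated models.

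Two practical objections have weight. With more than 30 centres and about 187 expected events, extra terms raise questions of sparse data and missing covariates, and centre was not in the simulations. The low cost of useless covariates answers this only in part. Also, the Intervention section places the recording of pre-intervention observations after randomisation, by a team that knows the allocation, so that FiO2 value may not be a true baseline.

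Finally, the statistical analysis plan is not shown and may already add covariates. The point rests on what the article fixes: the primary covariate set and the stated reason for the secondary adjustment.

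**Conclusion.** The point holds as a missed efficiency gain of modest size. The primary analysis is valid, and the planned sample size delivers its stated power. Pre-specified adjustment would add about 1 to 3 points of power at 38% versus 25%, and about 1.5 to 8 points at 38% versus 28%.

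These ranges assume a covariate score with an AUC of about 0.64 to 0.73 for death or BPD beyond what the model already holds, and no loss from the centre terms. The upper ends need a combined score of a strength that the article does not document. FiO2 alone would give about 1 point at the planned effect and about 2 at the smaller one, or less after range restriction. The change is worth making because it costs little and helps most if the true effect is smaller than planned.

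**What to change.** Before unblinding, in the analysis plan:

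- Name a short covariate set for the primary model, included whatever the observed balance: gestation in weeks or days, birth weight, sex, antenatal steroids and FiO2 at qualification, alongside centre.
- Define that FiO2 as a value fixed before randomisation. If the trial forms hold only the pre-intervention reading, capture or retrieve the qualifying value.
- Derive the marginal risk difference and risk ratio from the adjusted model by standardisation, so that the reported effect does not depend on the covariate set for its meaning.
- Keep the strata-only model as a sensitivity analysis, and drop the chance-imbalance rationale with the models built on it.
- State how small centres are handled in the primary model, and how a missing covariate is handled.

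The cost is mainly wording, with no added recruitment. The drawbacks are an odds ratio conditional on more covariates, which standardisation addresses, and the need for the two handling rules.
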